#### **4.4 Subject Withdrawal**

Subject withdrawal refers to voluntary study withdrawal due to the subject's inability to participate in the scheduled visits (AE/non-AE) or the inability to contact the subject during the visit scheduled by the study protocol.

Subjects will be informed that they have the right to withdraw from the study at any time and withdrawn subjects will not be replaced.

The investigator should try his/her best to reach the subjects who are unable to return for a visit at the scheduled time. All data should be collected from the subjects before the day of withdrawal for subsequent analysis. The date and possible reason for withdrawal should be documented in the source record and case report form (CRF):

- SAE (name)
- Non-SAE (name)
- Protocol violation (detailed description)
- Informed consent withdrawal not caused by AE
- Departure from the location of the study site
- Loss to follow-up
- Death (collection of relevant information and certificate of the cause of death)
- Other (detailed description)

### **5. PROTOCOL VIOLATIONS AND DEVIATIONS**

#### **5.1 Protocol Violations**

- ✓ The investigator did not perform proper informed consent process with the subject;
- ✓ the investigator has violated the inclusion/exclusion criteria and enrolled ineligible subjects;
- ✓ the investigator has immunized the subject with a vaccine of the wrong arm or number;
- ✓ the investigator has immunized the subject with an improperly stored vaccine;
- ✓ other circumstances judged by the investigator that significantly impact the immunogenicity and safety assessments of the vaccine.

The investigator should immediately report protocol violations to the principal investigator and sponsor, pay close attention to the involved subjects, collect safety information, ensure the subjects' safety, and record the events in detail. Subjects with protocol violations can be withdrawn from the study upon the judgment of the principal investigator and sponsor.

## **5.2 Protocol Deviations**

- ✓ Procedures are completed beyond the set time window (+ 14 d for blood collection);
- ✓ subject has poor adherence;
- ✓ subject has not completed blood sample collection;
- ✓ subject has taken prohibited medications (received  $\geq 2$  mg/kg/d intramuscular, oral or intravenous systemic corticosteroids for  $\geq 14$  d or other immunosuppressants);
- ✓ insufficient time since immunization with other vaccines.

The investigator should record all protocol deviations in detail and report them to the principal investigator and sponsor. The principal investigator and sponsor will then determine whether the subject can proceed with the rest of the study. In addition, the principal investigator should assess the subject's data to determine whether they can be included in the safety or immunogenicity analysis.

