## **3. TRIAL DESIGN**

### **3.1 Design**

This trial uses a randomized, controlled, open-label design to evaluate the safety and immunogenicity of the booster dose of co-purified DTaP or DT at children aged 6 years.

This study plans to enroll 480 subjects who will be randomized into 2 groups with 240 subjects per group.

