### **Per-protocol set (PPS):**

The PPS is a subset of the FAS that contains subjects with better protocol adherence. All subjects who conform to the inclusion/exclusion criteria, have completed all visits as required by the protocol, and were not removed after blinded review of the serology results are included in the PPS.

Subjects who meet the following conditions are not included in the PPS:

- Subjects without valid pre- and post-immunization antibody titer values;
- subjects with incomplete immunization;

- subjects with blood samples collected beyond the set time window;
- subjects immunized with the wrong vaccine;
- received immunoglobulin injection or whole blood/plasma infusion after immunization to post-immunization blood collection.

PPS is the primary analysis set in this study. Explanation is required if inconsistency is identified between the FAS and PPS.

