**Safety set (SS):**

All randomized subjects who have been immunized with one dose of the investigational vaccine and have at least one safety assessment are included in the SS. The SS is primarily used for the analysis of vaccine-related AEs, SAEs, and concomitant medications.

[figure not shown]

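### Section 5.2 lets the principal investigator decide, without criteria or blinding, whether a child with a protocol deviation enters the safety analysis, which conflicts with the section 6 safety set

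*Combined protocol and SAP*

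**What the plan says.** Three parts of the combined protocol and SAP bear on this.

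- **Section 5.2, Protocol Deviations**, lists five kinds of deviation: a procedure outside its time window, poor adherence, a blood sample not obtained, use of prohibited immunosuppressive medication, and too short an interval from another vaccine. The principal investigator and sponsor together decide whether the child continues. A separate sentence then says that "the principal investigator should assess the subject's data to determine whether they can be included in the safety or immunogenicity analysis". The sponsor has no part in that second decision, and no criterion or timing is given for it.
- **Section 6, Safety set (SS)**, is a rule: "All randomized subjects who have been immunized with one dose of the investigational vaccine and have at least one safety assessment are included". It contains no exception for deviations or violations.
- **On blinding**, section 3.1 states: "This trial uses a randomized, controlled, open-label design". The only blinded step named for forming an analysis set is in the per-protocol set (PPS) definition, which covers children who "were not removed after blinded review of the serology results are included in the PPS". It concerns serology and does not extend to the safety set.

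**The concern.** The same child can be in the safety set by rule and in it only by judgement. A statistician building the SS from section 6 and one following section 5.2 could arrive at different denominators and different event counts, and the plan does not say which text governs.

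The discretionary route is the riskier one. The person deciding is told to look at the child's data, may know which vaccine was given, and has no written standard to apply. Some triggers may also be related to harm. A child who reacts badly may miss the day 28 blood draw or comply poorly, and section 4.4 itself recognises that an adverse event can be why a child cannot attend visits. Leaving such children out could make a vaccine look better tolerated than it was, and by different amounts in the two arms. The synopsis names safety alongside immunogenicity in the study objective, so this affects a main purpose of the trial.

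**Working it through.** The plan states no figure on this point, so the check is mainly a comparison of texts.

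**Step 1. Does any listed deviation affect SS membership under section 6?** Membership needs (a) randomisation, (b) immunisation with one dose and (c) at least one safety assessment.

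| Deviation in section 5.2 | Bears on (a), (b) or (c)? |
|---|---|
| Procedure outside its window (the example given is blood collection) | No |
| Poor adherence | Only if it leaves the child with no safety assessment at all; the SS rule then already excludes the child |
| Blood sample not completed | No |
| Prohibited corticosteroids or other immunosuppressants | No |
| Too short an interval from another vaccine | No |

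No row needs a judgement by the principal investigator to settle SS membership. Where the rule and the judgement agree, the judgement adds nothing. Where they differ, section 6 is contradicted.

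**Step 2. Is the decision shielded from knowledge of arm or outcome?** Section 3.1 makes the trial open-label. The blinded review in section 6 is tied to serology and the PPS. Section 5.2 mentions no blinding and directs attention to the child's data without limiting which data. No shield is stated.

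**Step 3. How far could a few exclusions move a rate?** The planned size is 240 per arm (section 3.1). The event counts and numbers excluded below are assumptions, since the documents give no adverse event counts. If x children have an event and k of those are left out, the rate changes from x/240 to (x − k)/(240 − k).

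| x | Rate, all 240 | k | Rate after exclusion |
|---|---|---|---|
| 5 | 5/240 = 2.1% | 2 | 3/238 = 1.3% |
| 5 | 5/240 = 2.1% | 3 | 2/237 = 0.8% |
| 12 | 12/240 = 5.0% | 3 | 9/237 = 3.8% |
| 24 | 24/240 = 10.0% | 3 | 21/237 = 8.9% |

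If both arms truly had 5 events and two affected children were left out of one arm only, an apparent difference of 2.08% − 1.26% = 0.82 percentage points would arise from selection alone. If the three children left out had no event, the rate would hardly change: 5/237 = 2.1%. The harm therefore depends on who is left out, and section 5.2 leaves that open.

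**The case against.** **The two sections might be compatible.** Section 5.2 could be read as asking the principal investigator only to sort deviating children into the sets that section 6 defines, for instance by checking that a safety assessment exists. That would remove the contradiction and leave only missing detail. The wording does not support it well: it describes a decision on whether the child's data can be included, does not refer to the section 6 definitions, and covers deviations that have no bearing on them.

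**Some deviations do matter for safety.** Immunosuppressive treatment or a recent other vaccine can confuse the attribution of an event. That is true, but it is a reason to flag those children or run a sensitivity analysis. It does not justify open discretion to leave them out of a set defined by vaccination.

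**The bias is not certain, and its direction is not fixed.** This stands. Reported rates fall only if the children left out had more events than the rest, and nothing in the documents shows that.

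Two stronger readings are tempting and are not supported:

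- A reader might infer that section 5.1 also allows children to be dropped from the safety analysis, because it says that "Subjects with protocol violations can be withdrawn from the study upon the judgment of the principal investigator and sponsor". That is withdrawal from the study, not removal from an analysis set. The same paragraph requires the investigator to "pay close attention to the involved subjects, collect safety information, ensure the subjects' safety, and record the events in detail", and section 4.4 adds: "All data should be collected from the subjects before the day of withdrawal for subsequent analysis". With no exception in the SS definition, a randomised, vaccinated child with a violation and one safety assessment stays in. At most, withdrawal could shorten later safety follow-up.
- A reader might take Supplementary Table 1, whose denominators are 234 and 224 against a target of 240 per arm, as a count of affected children. It is a serology table. It says nothing about SS membership, and the documents available give no reasons for those absences.

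**Conclusion.** The point holds for section 5.2 against section 6. As written, the plan permits a criterion-free, unblinded decision by the principal investigator on whether a child with a deviation counts in the safety analysis, while the SS definition already counts every such child who was randomised, immunised and assessed at least once. Section 5.1 is not part of the defect.

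This is a finding about what the text allows. The documents do not show that the discretion was used or that any child was left out of the safety set, so no actual bias can be claimed or sized. The illustration rests on assumed event counts and the planned 240 per arm. It shows only that two or three exclusions of affected children can change a low event rate noticeably, and a rate near 10% much less.

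The conflict should be corrected: it leaves the safety denominator undetermined, and removing it is easy.

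**What to change.** 1. In the last sentence of section 5.2, delete the words *safety or*, so that the principal investigator's assessment concerns immunogenicity only.
2. In section 6, under the safety set, add a sentence such as: *No protocol deviation or violation removes from the SS a subject who meets its definition; data collected up to any withdrawal are kept, as section 4.4 provides.* Section 5.1 counts a faulty consent process as a violation, so if data obtained without valid consent may not be used, say so as a separate, explicit exception.
3. Optionally, state that the SS is analysed by the vaccine actually received. Section 5.1 foresees a child being given the other arm's vaccine and the PPS excludes such children, but the SS definition does not say under which vaccine they count.

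The withdrawal rule in section 5.1 need not change. The cost is a few words in two sections, with no added data, visits or procedures.

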## **6. ANALYSIS SETS**

### **Full analysis set (FAS):**

The FAS is the ideal subject population determined based on the intention to treat (ITT) principle, which includes all randomized subjects who have received at least one dose of the vaccine and have valid pre-immunization antibody titer results.

### **Per-protocol set (PPS):**

The PPS is a subset of the FAS that contains subjects with better protocol adherence. All subjects who conform to the inclusion/exclusion criteria, have completed all visits as required by the protocol, and were not removed after blinded review of the serology results are included in the PPS.

Subjects who meet the following conditions are not included in the PPS:

- Subjects without valid pre- and post-immunization antibody titer values;
- subjects with incomplete immunization;

- subjects with blood samples collected beyond the set time window;
- subjects immunized with the wrong vaccine;
- received immunoglobulin injection or whole blood/plasma infusion after immunization to post-immunization blood collection.

PPS is the primary analysis set in this study. Explanation is required if inconsistency is identified between the FAS and PPS.

**Safety set (SS):**

All randomized subjects who have been immunized with one dose of the investigational vaccine and have at least one safety assessment are included in the SS. The SS is primarily used for the analysis of vaccine-related AEs, SAEs, and concomitant medications.

[figure not shown]

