#### Solicited AEs:

All solicited AEs observed within 7 d of immunization are assumed by default to be related to the vaccine. The relationship between all unsolicited AEs/SAEs and the vaccines will be determined by the investigator.

✓ Local reactions

Pain, induration, swelling, rash, redness, and pruritus.

Systemic reactions

Fever, fatigue/weakness, decreased appetite, nausea, vomiting, diarrhea, allergy, myalgia, and arthralgia.

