### 3.6 Causality Assessment of Adverse Event

The investigator should have measures in place to judge the causal relationship between solicited/unsolicited AEs and immunization, to identify immunization-related SAEs, and to suspend or terminate the clinical trial in a timely manner in order to minimize damages to the subjects.

General rules for causality assessment:

- ✓ **Definitely related:** Evidence of investigational vaccine immunization; AE follows a reasonable temporal sequence from immunization with the investigational vaccine; occurrence of AE is more reasonably explained by the investigational vaccine than other reasons; AE is observed after repeated immunization with the investigational vaccine; AE is consistent with what is known about this type of vaccine.
- ✓ **Probably related:** Evidence of investigational vaccine immunization; AE follows a reasonable temporal sequence from immunization with the investigational vaccine; occurrence of AE is more reasonably explained by the investigational vaccine than other reasons.
- ✓ **Possibly related:** Evidence of investigational vaccine immunization; AE follows a reasonable temporal sequence from immunization with the investigational vaccine; occurrence of AE may be explained by the investigational vaccine or other reasons.
- ✓ **Possibly unrelated:** Evidence of investigational vaccine immunization; AE is more likely caused by other reasons; AE is absent or undetermined after repeated immunization.
- ✓ **Definitely unrelated:** Absence of investigational vaccine immunization; or AE does not follow a reasonable sequence from immunization with the investigational vaccine; or AE is caused by other obvious reasons.

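### The safety summary centres on investigator-attributed, vaccine-related AEs in an open-label trial; an all-cause comparison by arm should lead

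*Combined protocol and SAP*

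**What the plan says.** - **Use of the safety set.** Section 6, Safety set (SS): "The SS is primarily used for the analysis of vaccine-related AEs, SAEs, and concomitant medications". No comparison of all AEs regardless of cause is named there. Entry requires having been "immunized with one dose of the investigational vaccine", plus at least one safety assessment.
- **Blinding.** Section 3.1: "This trial uses a randomized, controlled, open-label design". The only blinded step mentioned is the serology review in the per-protocol set definition, which does not concern AEs.
- **Causality under the Solicited AEs heading (Section 3.4).** "All solicited AEs observed within 7 d of immunization are assumed by default to be related to the vaccine". For the rest: "The relationship between all unsolicited AEs/SAEs and the vaccines will be determined by the investigator".
- **Causality under Section 3.6.** "The investigator should have measures in place to judge the causal relationship between solicited/unsolicited AEs and immunization". A five-level scale follows. *Definitely related* lists "AE is observed after repeated immunization with the investigational vaccine". *Possibly unrelated* lists "AE is absent or undetermined after repeated immunization".
- **Data collected.** Section 3.4 has both arms record every solicited and unsolicited AE on daily diary cards from D0 to D28, with passive SAE collection at 6 months.

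**The concern.** Safety is a stated objective, and the trial has a randomised, vaccinated control arm followed with the same diary. Ordinary childhood illness over 28 days should balance between arms in expectation, so counting every AE by arm gives a comparison that needs no causal judgement. If events are first filtered by relatedness, and the person judging knows which vaccine was given, a difference in labelling habits becomes a difference between arms. It can create an apparent excess under DTaP, or hide a real one.

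The rules behind the label are also unsettled. Two sections treat solicited AEs differently, and two of the five causality levels refer to repeat immunization although each child receives one study dose.

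**Working it through.** **1. Which events are exposed to labelling**

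| Events | Solicited AEs heading | Section 3.6 | Does the related count depend on investigator judgement? |
|---|---|---|---|
| Solicited, within 7 days | related by default, both arms | investigator judges | only if 3.6 overrides the default |
| Solicited, days 8–28 | no rule | investigator judges | yes |
| Unsolicited | investigator decides | investigator judges | yes |
| SAEs | investigator decides | investigator judges | for attribution, yes; the SAE count need not be filtered |

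The text does not say which section governs in the first row.

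**2. The repeat-immunization clauses**

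Each child gets one study dose. Recurrence after repeated immunization cannot be shown within the trial, so *Definitely related* is out of reach if every listed condition must be met. An outcome that is undetermined after repeat immunization is the situation for every AE here, so that clause under *Possibly unrelated* does not separate one event from another. *Probably related* and *Possibly related* contain no such clause and remain usable.

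**3. The plan's own figure**

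The documents give no AE rate, safety margin or safety power to reproduce. The one relevant figure is the denominator: 240 per group (Section 3.7), consistent with 60 blocks × 8 = 480. It comes from the pertussis seroconversion target of 70%. The expected rate is not stated, so 240 cannot be derived from the stated inputs alone. Assuming 80%:

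n = [1.960√(0.70 × 0.30) + 1.282√(0.80 × 0.20)]² / 0.10² ≈ 200, and 200 / 0.85 ≈ 236, close to 240.

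The sample size was therefore not set for safety. I use 240 per arm below.

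**4. What differential labelling could do**

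Assumptions, none from the documents: the same true proportion p of children in each arm has an AE of a type that needs a causal judgement; shares q₁ (DTaP) and q₂ (DT) are labelled related. The observed related rates are then p·q₁ and p·q₂.

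The chance that a two-sided 5% chi-square comparison shows a difference was found by exact enumeration over 240 versus 240. The normal approximation for p = 20%, labelled 60% versus 40%, runs as follows:

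- related rates: 0.20 × 0.60 = 0.12 and 0.20 × 0.40 = 0.08, difference 0.04
- null SE = √(2 × 0.10 × 0.90 / 240) = 0.0274; critical difference = 1.960 × 0.0274 = 0.0537
- SE under the alternative = √[(0.12 × 0.88 + 0.08 × 0.92) / 240] = 0.0273
- Φ[(0.04 − 0.0537) / 0.0273] = Φ(−0.50) ≈ 0.31, matching the enumeration

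| True AE rate, both arms | Labelled 60% vs 40% | Labelled 80% vs 40% | Labelled 50% vs 50% | All-cause |
|---|---|---|---|---|
| 5% | 10% | 25% | 4.9% | 4.8% |
| 10% | 17% | 46% | 4.8% | 4.9% |
| 20% | 31% | 78% | 4.9% | 5.0% |
| 30% | 45% | 93% | 5.0% | 5.0% |

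Entries are the chance of a false difference. It exceeds 5% only when labelling differs by arm.

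**5. Dilution by default-related reactions**

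If a proportion s of each arm has a default-related solicited reaction, independent of the other events, the pooled related rate is 1 − (1 − s)(1 − p·q). Take p = 10%, labelled 80% versus 40%, and s = 20%:

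- DTaP: 1 − 0.80 × 0.92 = 26.4%
- DT: 1 − 0.80 × 0.96 = 23.2%

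The chance of a false difference falls from 46% to 13%. For s = 10%, 30% and 40% it is 19%, 10% and 8%.

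**The case against.** The Section 6 sentence belongs to an analysis-set definition. It says what the set is mainly for and excludes nothing, and since every AE is recorded an all-cause table can be produced. This stands as far as it goes: the data exist, but the supplied text does not make that table the main one.

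The default rule protects the core reactogenicity data, because labelling cannot separate the arms when all early solicited AEs count as related in both. This stands if the default governs. The two sections can be read together, with 3.6 as a general duty and the default as the specific rule, but the text does not say so.

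A reader might infer several stronger things that the documents do not support:

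- *The whole between-arm safety result could be manufactured by labelling.* The exposure is limited to the rows marked in the table of events, and pooling with default-related reactions shrinks it.
- *Days 8–28 solicited AEs have no rule at all.* Section 3.6 can cover them.
- *No AE can be called related after one dose.* Two related levels remain available. The four earlier doses required at inclusion do not clearly settle the repeat-immunization clause either: they are not stated to be the study product, and the supplied text collects no reactions to them.
- *DT-arm AEs are unrelated by definition*, because DT might not be the investigational vaccine. The term is not defined, and an undefined term does not establish that reading.
- *All-cause counts are unbiased.* Diaries are completed with the arm known, so reporting itself may differ.
- *A confirmatory safety error rate is inflated.* The stated hypotheses and outcomes concern immunogenicity, and no safety test or margin is given. Part of the text before Section 3 and a figure after the safety set definition are missing from the supplied text, so one cannot be ruled out.

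**Conclusion.** The concern holds in limited form. Section 6 directs the safety set mainly to vaccine-related AEs. For unsolicited AEs, solicited AEs on days 8 to 28 and SAE attribution, that label comes from investigators not described as blinded. Solicited AEs within 7 days are protected only if the default rule takes precedence over Section 3.6. The repeat-immunization criteria do not fit a one-dose trial, though this does not prevent an AE from being classed as related and does not by itself favour an arm.

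The size of any distortion is unknown. The 10% to 45% range assumes equal true AE rates of 5% to 30%, labelling of 60% versus 40%, 240 analysed per arm and a nominal 5% comparison that the plan does not itself state. It shows how sensitive the related-AE comparison would be and does not predict what happened in this trial. The change is worth making because it costs little and uses data already collected.

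**What to change.** 1. In Section 6 (SS), make the main safety summary all AEs regardless of causality, by arm, each with a difference and 95% CI: solicited AEs D0–D7, all AEs D0–D28, and SAEs to 6 months. Show vaccine-related AEs as a secondary table.
2. Reconcile the Solicited AEs text with Section 3.6, so that one stated rule applies to solicited AEs in each window (within 7 days, and days 8–28).
3. Reconcile the repeat-immunization criteria in Section 3.6 with the one-dose design.

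The cost is protocol and SAP wording, one extra table, and somewhat higher reported AE percentages in both arms. The change removes dependence on investigator attribution from the main summary. It does not remove open-label bias in diary reporting, which should be stated as a limitation.
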